**Table 3: Scoring for Severity of Systemic Solicited Adverse Events**

|                                                                                      | Score/Grade        |
|--------------------------------------------------------------------------------------|--------------------|
| Fever (axillary temperature measured once daily even in the absence of signs) |                    |
| <38°C                                                                                | 0                  |
| 38°C to <39°C                                                                        | 1                  |
| 39°C to <40°C                                                                        | 2                  |
| ≥40°C                                                                                | 3                  |
| Headache, Malaise, Myalgia, Arthralgia, Nausea and Vomiting                   | Score/Grade |
| Absent                                                                               | 0                  |
| Present, but easily tolerated                                                        | 1                  |
| Discomforting enough to interfere with normal activities                             | 2                  |
| Disabling, prevents normal daily activity, requires bed rest and treatment           | 3                  |

### 7.2.3 Assessment of Unsolicited Adverse Events

- During the first 28 days after each dose of the assigned vaccine, the subject will record any unsolicited AEs in the subject diary card.
- These unsolicited AEs will be reviewed and transcribed onto the Adverse Event CRF pages by the Investigator, using appropriate medical terminology and appropriate scoring for severity of AE (as applicable).

### 7.2.4 Assessment of Any Serious Adverse Event (SAE)

- During the entire study period (from study inclusion till last follow-up visit i.e. till Day 365), the Investigator will record and report all Serious Adverse Events (SAEs); whether or not related to the vaccination.

### 7.2.5 Assessment of Severity for all Unsolicited Adverse Events (including any Serious Adverse Events)

The Investigator will record, report and grade the following unsolicited AEs on the Adverse Event CRF pages, using medical language and as per Table 4: Scoring for severity of systemic unsolicited Adverse Events:

*Information contained in this publication is the property of EVI and ICGEB and is confidential and will not be disclosed to third parties without written authorization from EVI and ICGEB. No part of this document may be reproduced, stored in a retrieval system or transmitted in any form or by any means -electronic, mechanical, recording or otherwise - without the prior authorization of EVI and ICGEB*

[figure not shown][figure not shown]

- All unsolicited adverse events that occurred during the first 28 days following each dose of the vaccine, and
- All Serious Adverse Events during the entire study period (from study inclusion till last follow-up visit)

| Table 4: Scoring for severity of systemic unsolicited Adverse Events |                    |
|-----------------------------------------------------------------------------|--------------------|
| Unsolicited Adverse Event Characteristics                            | Score/Grade |
| Sign or symptom present, but easily tolerated                               | 1                  |
| Discomforting enough to interfere with normal activities                    | 2                  |
| Disabling, incapacitating with inability to perform usual activity          | 3                  |

### 7.2.6 Other Clinical Safety Assessments

- During the entire study period (from study inclusion till last follow-up visit), the Investigator will also record details of all the concomitant medications taken.
- During each visit the investigator will perform a complete physical examination (including general examination for temperature, lymphadenopathy and other local or systemic signs and symptoms).
- In addition, on Days 14, 42 and 194, the investigator will specifically check for the presence of a nodule at the injection site. The size, localisation and outcome of the lymph nodes will be recorded on the CRF pages, as well as the size and outcome of the nodule if any.

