### 6.1 Preparation and Administration of Study Vaccines

Both the investigational and control vaccines will be administered intramuscularly in the non-dominant deltoid for the first and third administration. The second administration will be performed in the dominant deltoid. Since this is a single-blind study, care will be taken that the identity of the assigned vaccine is not disclosed even inadvertently to the subject.

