#### C. Vaccination Schedule

*Information contained in this publication is the property of EVI and ICGEB and is confidential and will not be disclosed to third parties without written authorization from EVI and ICGEB. No part of this document may be reproduced, stored in a retrieval system or transmitted in any form or by any means -electronic, mechanical, recording or otherwise - without the prior authorization of EVI and ICGEB*

[figure not shown][figure not shown]

The vaccine will be administered as per a 3-dose vaccination schedule on Days 0, 28 and 180

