#### ***7.2.2.2 Solicited AEs by Investigator's Assessment***

The Investigator will do an independent assessment of the local and systemic signs and symptoms 14 days after each vaccination (i.e. on Days 14, 42 and 194),

- During these visits, the investigator will perform a complete physical examination (including general examination for temperature, lymphadenopathy and any other local or systemic signs and symptoms).
- In addition, the investigator will specifically check for the presence of a nodule (10) at the injection site. The size and outcome of the nodule (if any) will be recorded on the CRF pages, as well as the size, localisation and outcome of the local lymph nodes.
- The investigator will independently evaluate the subjects for solicited AEs on Days 14, 42 and 194.
- The above-mentioned local symptoms and signs (solicited AEs) will be graded on the CRF by the Investigator on Days 7, 14, 35, 42, 187 and 194 as per Table 2: Scoring of Severity of Local Solicited Adverse Events and Table 3: Scoring for Severity of Systemic Solicited Adverse Events

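### Injection-site nodules have a dedicated check only 14 days after each dose, and none just before dose 3 in the arm already used for dose 1, so late nodules may be under-recorded and some Day 194 nodules may be ambiguous between doses

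*Supplement*

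**What the plan says.** **The nodule check.** Section 7.2.6 of the protocol states that at each visit "the investigator will perform a complete physical examination (including general examination for temperature, lymphadenopathy and other local or systemic signs and symptoms". It then adds a targeted check: "In addition, on Days 14, 42 and 194, the investigator will specifically check for the presence of a nodule at the injection site". Section 7.2.2.2 says the same of the visits 14 days after each dose: "the investigator will specifically check for the presence of a nodule (10) at the injection site".

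**What is recorded.** One sentence in section 7.2.6 covers the lymph nodes first and, at its end, any nodule found: "The size, localisation and outcome of the lymph nodes will be recorded on the CRF pages, as well as the size and outcome of the". Localisation is asked for the lymph nodes, not for the nodule. Section 7.2.2.2 makes the same distinction.

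**Dosing days and arm.** Section 6.1.1.3 states: "The vaccine will be administered as per a 3-dose vaccination schedule on Days 0, 28 and 180". Section 6.1 assigns the arms: "Both the investigational and control vaccines will be administered intramuscularly in the non-dominant deltoid for the first and third administration", and "The second administration will be performed in the dominant deltoid".

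**Other routes of capture.** The diary items in section 7.2.2.1 include swelling and induration for 14 days after each dose, but not nodule. Table 2 has no nodule grade. Sections 7.2.3, 7.2.5 and 8.4.2 have non-serious unsolicited events reported for 28 days after each dose. Tables 1 and 7 mark unsolicited events at every visit from Day 0 to Day 208 but not at Day 365. The Day 365 list in section 7.4.3.14 names only serious events. The Day 180 list in section 7.4.3.10 also names only serious events, although both tables mark unsolicited events there.

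**The concern.** Safety is the primary objective of this first-in-human study. Local reaction at the injection site is the only toxicity that section 2.4 reports from the animal work with this emulsion. The protocol singles out nodules for a targeted check in addition to the general examination, so it does not treat the two as equivalent. Yet it takes no targeted reading later than 14 days after any dose.

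Two things follow. A nodule that appears or persists after that reading depends on an unprompted finding at a general examination, made by staff who know the allocation (section 4.5), and for long stretches no entry is required. Also, dose 3 goes into the deltoid that received dose 1. Without a required reading just before that injection, a nodule found there on Day 194 has no documented comparison.

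**Working it through.** The plan states no figure to reproduce here. The check is day arithmetic on the schedule.

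**Inputs.** Doses on Days 0, 28 and 180 (6.1.1.3); non-dominant deltoid for doses 1 and 3, dominant for dose 2 (6.1); targeted checks on Days 14, 42 and 194 (7.2.6); examination visits on Days 0, 7, 14, 28, 35, 42, 56, 180, 187, 194, 208 and 365 (Tables 1 and 7); non-serious event window of 28 days after each dose (7.2.5, 8.4.2).

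**1. Timing of the checks.** 14 − 0 = 14, 42 − 28 = 14 and 194 − 180 = 14 days after the dose. Of the 12 examination visits from Day 0, 9 have no targeted check: Days 0, 7, 28, 35, 56, 180, 187, 208 and 365.

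**2. Intervals without a targeted check.**
- Between any two successive checks: 194 − 42 = 152 days.
- From the check that follows dose 1 to dose 3 in the same deltoid: 180 − 14 = 166 days; to the next check that follows a dose in that deltoid: 194 − 14 = 180 days. If the Day 42 check is read as covering both arms, the latter falls to 152 days.
- From the check that follows dose 2 in the dominant deltoid to the end of study: 365 − 42 = 323 days.
- From the last check to the end of study: 365 − 194 = 171 days.

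**3. What the adverse event windows cover.** They run over Days 0–28, 28–56 and 180–208. The first two join as Days 0–56 (57 days) and the third has 29 days, giving 57 + 29 = 86 of the 366 days from Day 0 to Day 365. Uncovered are Days 57–179 (179 − 57 + 1 = 123 days) and Days 209–365 (365 − 209 + 1 = 157 days), 280 days in all. The ±1-day visit windows move these limits only slightly.

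**4. The visits that matter, side by side.**

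| Day | General examination | Targeted nodule check | Onset since previous visit inside a 28-day window? | Unsolicited events marked in Tables 1 and 7 |
|---|---|---|---|---|
| 28, before dose 2 | yes | no | yes | yes |
| 56 | yes | no | yes | yes |
| 180, before dose 3 | yes | no | no | yes, but the visit list names only serious events |
| 194 | yes | yes | yes | yes |
| 208 | yes | no | yes | yes |
| 365 | yes | no | no | no |

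On Days 28, 56 and 208 a nodule has a route into the data as an unsolicited event. On Day 180 the route is unclear, and absence of a nodule need not be documented. On Day 365 a newly found non-serious nodule has no required entry.

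**5. Effect of one misassignment.** With 10 test subjects per dosage, moving one subject's nodule from dose 1 to dose 3 changes that dosage's dose 3 proportion by 1/10 = 10 percentage points. This is the leverage of a single case, not an estimate of how often it happens.

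**The case against.** A reader might infer that later nodules are missed, that a Day 194 nodule cannot be assigned to a dose, and that the per-dose local safety profile is therefore wrong. The documents do not support any of these.

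- **Capture.** Local signs are part of the examination at every visit. Section 8.1 has the investigator ask about adverse events at each visit. Section 8.4.2 sends events found on examination within 28 days of a dose to the CRF. Subjects also record unsolicited events in the diary for those 28 days. It would be misleading to count only the three targeted visits as ascertainment.
- **Attribution.** Events are to carry start and end dates as far as possible (8.4.3). A nodule seen on Day 14 has its size and outcome recorded. The Day 180 list places the examination ahead of the injection. Confusion needs a dose 1 nodule that went unrecorded through the examinations on Days 28, 35, 42, 56 and 180 and was still present on Day 194.
- **Outcome.** Section 8.4.7 has adverse events followed until resolved or stable, so a nodule entered as an event does have follow-up.
- **Likelihood.** The acute animal reactions in section 2.4 were mild and subsided within three days in mice and three to six days in rats. The repeat-dose studies give no duration. Nothing in the documents shows nodules arising or lasting beyond two weeks.
- **Analysis.** Section 11.5.1.2 defines no per-dose nodule rate, and the detail is left to a separate SAP that is not shown.

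All of this stands and limits the point. It does not close the gap. Onset dates help only for nodules that were recorded, the 28-day windows end on Days 56 and 208, and neither the absence of a nodule before dose 3 nor its side is a required entry.

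**Conclusion.** The point holds as a limited weakness in the collection of primary safety data. If the protocol is followed exactly, a non-serious nodule starting on Days 57–179 or 209–365 falls outside required reporting, and the dose 3 site has no required nodule reading before injection. Late nodules may be under-recorded, and some Day 194 nodules may be ambiguous between doses 1 and 3.

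The size is unknown, because the documents give no frequency of late or persisting nodules. The 280 days measure the reporting gap, not the number of nodules lost.

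The conclusion assumes that the 28-day window applies separately to each dose, as sections 4.6.1, 7.2.3, 7.2.5 and 8.3 have it. The sentence in section 8.4.2 could also be read as one continuous period from the first dose to 28 days after the last. On that reading only Days 209–365 (157 days) would be uncovered, but the missing nodule reading before dose 3 would remain. The conclusion also assumes that the CRF, which is not shown, holds no more about nodules than the protocol names.

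The change is worth making because it is cheap and the readings cannot be recovered once the visits have passed. The gap does not make the safety results invalid.

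**What to change.** In sections 7.2.2.2 and 7.2.6 and in Tables 1 and 7, add a recorded nodule check to the existing physical examination on Days 28 and 180, before injection, and on Days 56, 208 and 365. For each deltoid injected so far, record presence or absence, arm and largest diameter. Name the arm as a CRF item at the existing checks on Days 14, 42 and 194 as well.

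Where nodules are reported by dose, in section 11.5.1.2 or the SAP, list separately any Day 194 nodule that was already present in that arm before dosing on Day 180.

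The cost is small, since no visit or examination is added. One deltoid is checked on Day 28 and two on each of the other four days: 1 + 2 + 2 + 2 + 2 = 9 short CRF lines per subject, or 9 × 45 = 405 if all 45 subjects complete the study.

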### 7.2.7 Laboratory Safety Assessments

Laboratory assessments will be done to assess biological safety at 28 days after each vaccination in reference with the baseline before the first dose, by measuring the following:

- Haematology: RBC count, Haemoglobin\*, Haematocrit/Packed Cell Volume (PCV), MCV (Mean Corpuscular Volume), MCH (Mean Corpuscular Haemoglobin), MCHC (Mean Corpuscular Haemoglobin Concentration), Platelet Count and Total Leukocyte Count (TLC) along with Differential Leukocyte Count (DLC) on Days -14, 28, 56, 180, 208, 365.

\*If the haemoglobin drops below 13 gm/dL, then a direct Coomb's test and a peripheral blood smear/film will be prepared and examined for evidence of possible haemolysis

*Information contained in this publication is the property of EVI and ICGEB and is confidential and will not be disclosed to third parties without written authorization from EVI and ICGEB. No part of this document may be reproduced, stored in a retrieval system or transmitted in any form or by any means -electronic, mechanical, recording or otherwise - without the prior authorization of EVI and ICGEB*

[figure not shown][figure not shown]

- Serum Chemistry: Potassium, Sodium, AST, ALT, Direct, Indirect and Total Bilirubin, Alkaline Phosphatase, Gamma Glutamyl Transpeptidase ( $\gamma$ GT), Creatinine, and Random blood glucose on Days -14, 28, 56, 180, 208, 365
- The total amount of blood sample required for these assessments across all visits would be approximately 60 ml.
- For all the laboratory evaluations, the investigator will receive the results/reports as per specified timelines from receipt of specimen at DLS (provided acceptable specimens and/or requisition forms have been obtained).
- The Sponsor's Medical Monitor will be alerted about any value significantly outside the normal range (Refer to the DLS Laboratory Manual for details).
- The screening (D-14 through D-1) and post-vaccination safety laboratory evaluations will be performed at the Central Laboratory at DLS, Mumbai, India.

**TABLE 5: SCHEDULE OF SAFETY LABORATORY EVALUATIONS**

| PARAMETERS                                                                                                                                                                                                                                 | VOLUME OF BLOOD |        |        |        |        |        |
|--------------------------------------------------------------------------------------------------------------------------------------------------------------------------------------------------------------------------------------------|-----------------|--------|--------|--------|--------|--------|
| VISITS                                                                                                                                                                                                                                     | V2              | V6     | V9     | V10    | V13    | V14    |
| DAYS                                                                                                                                                                                                                                       | D-14 to D-1     | D28    | D56    | D180   | D208   | D365   |
| Haematology: Haemoglobin, haematocrit (PCV), MCV, MCH, MCHC, RBC count, TLC, DLC, Platelet count                                                                                                                                    | 2 ml            | 2 ml   | 2 ml   | 2 ml   | 2 ml   | 2 ml   |
| Direct Coomb's Test (Peripheral Smear Test, as required)                                                                                                                                                                            | 2 ml            | 2 ml   | 2 ml   | 2 ml   | 2 ml   | 2 ml   |
| Serum Chemistry: Random blood glucose, sodium, potassium                                                                                                                                                                            | 5 ml            |        |        |        |        |        |
| Organ function tests:
Hepatic: Direct, indirect and total bilirubin, alanine-amino transferase (ALT/SGPT), aspartate-amino-transferase (AST/SGOT), alkaline Phosphatase and $\gamma$ GT
Renal: Serum creatinine |                 | 3.5 ml | 3.5 ml | 3.5 ml | 3.5 ml | 3.5 ml |
| Viral serology tests: HIV, HBs Ag and HCV                                                                                                                                                                                           |                 | ---    | ---    | ---    | ---    | ---    |

*Information contained in this publication is the property of EVI and ICGEB and is confidential and will not be disclosed to third parties without written authorization from EVI and ICGEB. No part of this document may be reproduced, stored in a retrieval system or transmitted in any form or by any means -electronic, mechanical, recording or otherwise - without the prior authorization of EVI and ICGEB*

[figure not shown][figure not shown]

### 7.3 Immunogenicity Assessments

The secondary immunogenicity endpoints of the present study will be assessed as follows:

- The humoral response to the candidate vaccine antigen will be assessed (quantitative assessment) by measuring the level of IgG antibodies developed against PfMSP-119 and PfF2 by ELISA on Days 0, 28, 56, 180, 208 and 365
- The humoral response to the candidate vaccine antigen will be assessed (qualitative assessment) to verify the ability of the IgG antibodies developed against PfMSP-119 and PfF2 to recognise the native protein on late stage *P. falciparum* schizonts and merozoites in vitro by IFA on Days 0, 28, 56, 180, 208 and 365.

The exploratory immunogenicity endpoints (for assessment of the quality of the humoral immune response) of the present study will be assessed as follows:

- IgG1, IgG2, IgG3, IgG4 subclasses by ELISA on samples obtained at Days 0, 28, 56, 180, 208 and 365.
- The ability of the IgG antibodies to block homologous and heterologous parasite growth in vitro by a *P. falciparum* blood-stage growth inhibition assay (GIA) against three parasite strains on samples obtained at D0, 56, 208 and 365

The immunogenicity laboratory evaluations will be performed at ICGEB, New Delhi, India.

| TABLE 6: SCHEDULE OF IMMUNOGENICITY LABORATORY EVALUATIONS                                                                                       |                 |       |      |       |      |       |       |
|--------------------------------------------------------------------------------------------------------------------------------------------------|-----------------|-------|------|-------|------|-------|-------|
| PARAMETERS                                                                                                                                       | VOLUME OF BLOOD |       |      |       |      |       |       |
| VISITS                                                                                                                                           | V1              | V3    | V6   | V9    | V10  | V13   | V14   |
| DAYS                                                                                                                                             | D-21 to D-14    | D0    | D28  | D56   | D180 | D208  | D365  |
| Serology (ELISA):
quantitative assessment- IgG antibodies developed against PfMSP-1 19 and PfF2 (including screening ELISA) | 4 ml            | 18 ml | 6 ml | 18 ml | 6 ml | 18 ml | 18 ml |
| Serology (IFA): qualitative assessment- IgG antibodies developed against PfMSP-1 19 and PfF2                                   | ---             |       |      |       |      |       |       |
| Serology (IgG subclasses by ELISA): IgG1, IgG2, IgG3, IgG4 subclasses                                                                     | ---             |       |      |       |      |       |       |
| Serology (GIA)                                                                                                                            | ---             |       | ---  |       | ---  |       |       |

Information contained in this publication is the property of EVI and ICGEB and is confidential and will not be disclosed to third parties without written authorization from EVI and ICGEB. No part of this document may be reproduced, stored in a retrieval system or transmitted in any form or by any means -electronic, mechanical, recording or otherwise - without the prior authorization of EVI and ICGEB

[figure not shown][figure not shown]

Approximately 4 ml of whole blood will be drawn at Visit 1 and 6 ml of whole blood at Visits 6 and 10. Approximately 18 ml of whole blood will be drawn to provide about 8-9 ml of serum for serology efficacy assessments at Visits 3, 9, 13 and 14. Thus, approximately 100 ml of whole blood sample will be drawn across all visits. The serum samples will be stored frozen at -70°C (with a temperature variation of +/- 10°C) before batch shipment to the laboratory for analysis. The measurements will be performed at ICGEB.

